**Methods:**

Eighty subjects will implement the program in a randomized order. The interventions for the control group mainly consisted of the routine distribution of health education materials and health education by holding health-themed lectures, and the preliminary proposed interventions including establishing management teams, regularly delivering related health knowledge, daily uploading of health intervention records, regular supervision and mutual encouragement, home visiting and psychological guidance. The primary outcomes are serum biomarkers such as alanine aminotransferase (ALT) and gamma-glutamyl transferase (GGT), aspartate aminotransferase, and imaging (liver ultrasound and magnetic resonance imaging). Second outcomes are: BMI, waist-to-hip ratio and quality of life. In addition, socio-demographic characteristics such as age, gender and ethnicity will be recorded. Children aged 7–18 years old and diagnosed with NAFLD will be included, patients will be not eligible if they do not agree to participate or are participating in other health intervention programs. This study was registered on ClinicalTrials.gov (NCT05527938).

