### Study design and setting

We will conduct a 1-year single-blinded randomized clinical trial. To recruit more study subjects, the study will conduct at a large hospital in Zhejiang Province (Figure 1).

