### Outcome

The primary outcome are serum biomarkers such as alanine aminotransferase (ALT) and gamma-glutamyl transferase (GGT). Second outcomes are: aspartate aminotransferase, and liver imaging (liver ultrasound and magnetic resonance imaging), BMI, waist-to-hip ratio and quality of life. In addition, socio-demographic characteristics such as age, gender, and ethnicity will be recorded. All outcomes were measured at baseline, week 4, week 16, week 24, week 36, and week 48 to determine the trajectory of change in outcome variables over intervention process.

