### Sample size

Sample size estimation will be performed using Professional Association for SQL Server (PASS) 2014 software for grasp degree analysis (Power Analysis). The mean effect size of the lifestyle intervention on the improvement of ALT indicators (Effect size) was estimated to be −1.35 according to the Meta-analysis of the clinical study conducted by Utz-Melere et al. (14, 15). The sample size required will be 32 study subjects per group by power analysis in reaching 80% effectiveness, using a two-tailed test with a test level of 0.05. Based on a 20% failure rate, this part of the study required 80 subjects, 40 in each group.

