### Statistical analyses

First, after eliminating the questionnaires that did not meet the requirements, all data will be organized and quantified and then entered the statistical software in pairs for analysis. Then statistical description of the data will be done, including descriptive statistical analysis of patients' general information, the mean and standard deviation will be used to describe the measurement data that conformed to normal distribution. Finally, statistical inferences will be made and *t*-test, ANOVA. The effect of the intervention on NAFLD w analyzed using McNemar's test for paired categorical data and χ^2^ or Fisher's exact test for independent categorical data, as appropriate. Changes in continuous variables will be analyzed using paired Student *t*-test. Statistical significance will be set at *P* < 0.05. Using analysis of covariance we evaluated whether baseline variables predicted changes in liver fat content and ALT during 6 months of treatment.

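### The primary claim is not reduced to one test: two unranked primary biomarkers, five follow-up visits, no primary visit and one blanket P < 0.05, against a sample size built on a single ALT test

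*Protocol article*

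**What the plan says.** - **Outcome.** The primary variables are introduced as "The primary outcome are serum biomarkers such as alanine aminotransferase (ALT) and gamma-glutamyl transferase (GGT"). AST, liver imaging, BMI, waist-to-hip ratio and quality of life are secondary. On timing: "All outcomes were measured at baseline, week 4, week 16, week 24, week 36, and week 48", with the purpose "to determine the trajectory of change in outcome variables over intervention process".
- **Abstract, Methods.** The primary list runs on beyond ALT to "gamma-glutamyl transferase (GGT), aspartate aminotransferase, and imaging (liver ultrasound and magnetic resonance imaging"). AST and imaging are thus primary here and secondary in the Outcome section.
- **Sample size.** The calculation concerns ALT only, with an effect size of −1.35, 80% power and 32 per group, "using a two-tailed test with a test level of 0.05". A 20% failure rate raises this to 40 per group. No visit is given, and no effect for GGT.
- **Statistical analyses.** The tests named include t-test, ANOVA, paired t-test for changes in continuous variables and ANCOVA. There is one level for all of them: "Statistical significance will be set at" P < 0.05. No repeated-measures model or single contrast across visits is named. The only time horizon in the section is in the ANCOVA that asks whether "baseline variables predicted changes in liver fat content and ALT during 6 months of treatment".
- **Study design and setting.** "We will conduct a 1-year single-blinded randomized clinical trial".

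**The concern.** A primary hypothesis needs a variable, a time point and, where there is more than one variable, a rule for what counts as success. The article attempts this definition and leaves all three parts open. The variable list is not closed and differs between the Abstract and the Outcome section. None of the five follow-up visits is singled out. Nothing says whether one marker suffices or both are needed.

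The sample size, by contrast, presumes one test of one marker at 0.05. A nominally significant ALT or GGT result at whichever visit looks best could later be presented as the primary result without contradicting anything written. The 5% error rate that the sample size relies on would then not describe the claim being made.

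**Working it through.** **1. The plan's own figures.** Inflation for failure reproduces: 32 / (1 − 0.20) = 40 per group. The 32 does not follow from the stated effect if −1.35 is read as a standardised difference: n = 2 × (1.960 + 0.842)² / 1.35² = 8.6, so 9 per group (10 with the t distribution). That mismatch is a separate point. What matters here is that the calculation uses one marker and one test at two-sided 0.05.

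**2. Size of the primary family.** Two markers (ALT, GGT) × five follow-up visits (weeks 4, 16, 24, 36, 48) = 10 possible comparisons. The Abstract's extra primaries are left out, and would enlarge the family.

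**3. Error if any one significant result counts, independent tests.** Formula: 1 − 0.95^k.

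| Rule | k | Type I error |
|---|---|---|
| One marker, one visit | 1 | 5.0% |
| Either marker, one visit | 2 | 9.75% |
| One marker, any visit | 5 | 22.6% |
| Either marker, any visit | 10 | 40.1% |

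**4. The same with correlation.** Repeated measurements on one child are correlated, and so are the two markers. The article gives no correlations, so these are assumptions: 0.3 to 0.9 between visits (equal, or decaying with distance between visits) and 0.3 to 0.9 between markers. For each setting, 400,000 sets of ten correlated null z-statistics were drawn, counting those with |z| > 1.96. Error for either marker at any visit:

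| Between-visit correlation | Equal; markers 0.3 | Equal; markers 0.9 | Decaying; markers 0.3 | Decaying; markers 0.9 |
|---|---|---|---|---|
| 0.3 | 36.6% | 28.1% | 38.0% | 29.4% |
| 0.5 | 32.4% | 24.7% | 35.3% | 27.1% |
| 0.7 | 26.8% | 20.2% | 30.6% | 23.2% |
| 0.8 | 23.2% | 17.3% | 27.0% | 20.3% |
| 0.9 | 18.7% | 13.9% | 21.7% | 16.1% |

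The range is about 14% to 38%, or 40% under independence. One marker over five visits gives about 10% to 22%. Either marker at one fixed visit gives about 7% to 9.6%, or 9.75% under independence.

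**5. After the fix.** ALT at one visit, with GGT tested only after a significant ALT result, holds the error for the pair at 5% or less. Alternatives: 0.025 for each marker at one visit gives 1 − 0.975² = 4.94% if independent, and requiring both markers to succeed also keeps it at or below 5%.

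**6. Does the fix cost patients?** ALT keeps the full 0.05 on which the sample size was based, so the calculation is unchanged. Even the costlier alternatives fit the stated effect. At 32 per group, 1.35 / √(2/32) = 5.40. Power is then Φ(5.40 − 2.241) = 99.9% at 0.025 and Φ(5.40 − 2.807) = 99.5% at 0.005 (ten-fold Bonferroni). This is for ALT; no GGT effect is given.

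**The case against.** The strongest reply is that the article never says each marker will be compared between arms at each visit, nor that any one significant result means success. It gives the repeated visits a descriptive purpose, the trajectory over time. The sample size points to ALT as the leading marker. Multiplicity rules are often left to a statistical analysis plan, and this is a condensed article.

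Most of this stands as a limit on the claim. A reader might infer that the trial's type I error is in fact several times 5%. The text does not support that: one prespecified visit for one marker, a single overall trajectory test, or a both-must-succeed rule would not produce those rates, and none of these is excluded. The absence of a multiplicity formula is likewise not the point.

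The objection does not supply the missing definition. The trajectory purpose is not matched by any trajectory test in Statistical analyses. ALT's role in the sample size does not rank it above GGT in the Outcome section. The Abstract and the Outcome section disagree on which variables are primary, and a later document cannot settle that without changing one of them.

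A second tempting inference is that the 6-month phrase sets a rival primary horizon, or adds to the error. It does neither. It belongs to an ANCOVA of baseline predictors of change, not to the comparison of arms, and week 24 is a scheduled visit of about that length. It sits awkwardly in a 1-year trial followed to week 48, and that is a wording point.

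**Conclusion.** The concern holds in conditional form. The article fixes the primary claim badly: two unranked markers in an open list, a different list in the Abstract, five visits with none primary, and one blanket level, against a sample size for a single ALT test. As written, nothing guarantees a 5% error rate for the primary claim. It could be about 7–10% if either marker at one visit counted, and about 14–40% if either marker at any visit counted. The lower ends rest on assumed correlations up to 0.9 and the upper ends on independence. Both ranges rest on an any-result-counts rule that the article neither states nor rules out.

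This should be settled before outcome data are examined by arm. The 6-month wording needs separate tidying and plays no part in these figures.

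**What to change.** 1. In Outcome and Statistical analyses, state one primary test: the between-arm difference in ALT at week 48, two-sided 0.05. ALT matches the basis of the sample size, and week 48 matches the length of the trial. The estimate could come from ANCOVA adjusted for baseline ALT, or from the week-48 contrast of a repeated-measures model. The latter is not named at present and would have to be added to Statistical analyses.
2. Test GGT at week 48 only if ALT is significant. Present all other visits as descriptive trajectory. One overall repeated-measures contrast, an alpha split or a both-must-succeed rule would also be valid if written down.
3. Delete *such as* from the primary outcome sentence, and bring the Abstract's primary list into line with the Outcome section.
4. Separately, label the 6-month baseline-predictor ANCOVA as a secondary week-24 analysis, or reconcile its wording with the 1-year design.

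**Cost.** A few sentences, plus a model specification if the repeated-measures route is chosen. Earlier visits lose confirmatory status and GGT is tested only conditionally. No extra patients are needed, because ALT keeps the full 0.05.

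### Six visits per child are meant to show a trajectory, but no test named for continuous outcomes, as written, compares trajectories between arms while allowing for within-child correlation

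*Protocol article*

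**What the plan says.** The protocol article's Outcome section names the primary outcomes: "The primary outcome are serum biomarkers such as alanine aminotransferase (ALT) and gamma-glutamyl transferase (GGT"). It sets one schedule for everything: "All outcomes were measured at baseline, week 4, week 16, week 24, week 36, and week 48". The reason given for the repeated visits is "to determine the trajectory of change in outcome variables over intervention process". Under Assignment of intervention, it is the children who are numbered and randomised, so each child contributes up to six values of each outcome.

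For continuous data the Statistical analyses section names three things:

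- a general statement, in an incomplete sentence: "Finally, statistical inferences will be made and *t*-test, ANOVA";
- a test for change: "Changes in continuous variables will be analyzed using paired Student" t-test;
- a prediction analysis: "Using analysis of covariance we evaluated whether baseline variables predicted changes in liver fat content and ALT during 6 months of treatment".

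For categorical data the section separates a test for paired data (McNemar) from tests for independent data (chi-squared or Fisher). It makes no such distinction for ANOVA. The article names no repeated-measures ANOVA, mixed model, generalised estimating equation or arm-by-visit term. The Discussion promises an intention-to-treat analysis and expects about 10% attrition; the Sample size section allows for 20%.

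**The concern.** The aim and the method do not meet. The paired t-test is the only test tied to change in continuous outcomes. It sets a child's value at one visit against the same child's value at another and does not compare arms. A fall in ALT in the intervention arm may be regression to the mean, since an elevated ALT is an entry criterion, or the effect of routine care that both arms receive. The ANCOVA asks which baseline variables predict change to 6 months; it is not described as an arm comparison, and the schedule runs to week 48.

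That leaves t-test and ANOVA. An unpaired t-test can compare arms at one visit but does not describe a trajectory. ANOVA could span the visits, but its validity depends on whether the six values from a child are treated as correlated, and the article does not say. At stake is whether the trajectory question gets a valid between-arm answer and whether children with incomplete follow-up contribute to it.

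**Working it through.** **1. What each named method can answer**

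| Method in Statistical analyses | Compares arms? | Uses all six visits? | Allows for within-child correlation? |
|---|---|---|---|
| Paired t-test on changes | No | No, two at a time | Yes, for that pair |
| t-test, if two-sample | Yes | No, one visit or one change | Not needed |
| ANCOVA of baseline predictors | Not described so | No, change to 6 months | Through the change score |
| ANOVA, type not stated | Possibly | Possibly | Only if the repeated-measures form |

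No row, as the article words it, gives yes in all three columns.

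**2. The plan's own figures**

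The Sample size section states that the effect on ALT "was estimated to be −1.35", with 32 per group, 80% power and two-sided 0.05. The dropout step reproduces: 32 / 0.8 = 40 per group, 80 in all. The 32 does not follow from 1.35 read as a standardised difference: 2 × (1.96 + 0.8416)² / 1.35² = 8.6, that is 9 per group, or 10 with the t correction. The effect that 32 per group detects with 80% power is about 0.71 SD. That mismatch is a separate matter, but because of it power is shown below at both values.

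**3. If ANOVA took the visits as independent rows**

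Assumptions: 32 completers per arm, unit SD, six visits, and an arm difference growing linearly to d at week 48. The article gives no within-child correlation, so 0.3 to 0.8 is assumed, under compound symmetry (CS) and first-order autoregression (AR(1)).

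*Pooled arm comparison.* The true variance of the difference in arm means exceeds the assumed one by the factor 1 + 5ρ under CS. The false-positive rate is therefore about P(|Z| > 1.96 / √(1 + 5ρ)).

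- ρ = 0.3: 1.96 / √2.5 = 1.24, about 22%
- ρ = 0.5: 1.96 / √3.5 = 1.05, about 29%
- ρ = 0.8: 1.96 / √5 = 0.88, about 38%

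Simulation (2,000 trials per setting) gave 23–37% under CS and 12–33% under AR(1), against a nominal 5%.

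*Arm-by-visit test.* Under CS the true variance of within-child contrasts is (1 − ρ), but the error term is about 1. The F statistic is therefore shrunk by (1 − ρ) and the test is conservative. Simulated false-positive rates were 1.1%, 0.1%, below 0.1% and below 0.1% at ρ = 0.3, 0.5, 0.7 and 0.8 under CS, and 3.5% down to 0.2% under AR(1).

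*Power of the arm-by-visit test at d = 0.71, CS*

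| ρ | Independent rows | Within-child error term |
|---|---|---|
| 0.3 | 33% | 61% |
| 0.5 | 23% | 76% |
| 0.7 | 11% | 95% |
| 0.8 | 8% | 99% |

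Check at ρ = 0.5: the linear differences 0, 0.083, 0.333, 0.5, 0.75 and 1 (times d) have a sum of squares about their mean of 0.745. The non-centrality is (32 / 2) × 0.71² × 0.745 / 0.5 = 12.0. On 5 and 310 degrees of freedom this gives 76% power, in agreement.

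Under AR(1) at d = 0.71, independent rows gave 23–39%, repeated-measures ANOVA 48–73% and a multivariate Hotelling test 30–42%.

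*Power at d = 1.35.* Independent rows kept 98–99.7% under CS and 90–94% under AR(1); repeated-measures ANOVA gave 96–100%.

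**4. If repeated-measures ANOVA was meant**

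The false-positive rate was 4.8–5.7% under CS and 5.7–8.1% under AR(1) without a sphericity correction. The classical form uses only children with all six visits. If 10–20% of 80 leave early, 8–16 children drop out of the analysis entirely, before any intermittent missed visits are counted.

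**The case against.** The strongest reply is that the article never says visits will be treated as independent. A reader might infer from unqualified ANOVA that the trial has committed itself to an analysis with a badly wrong error rate and little power. The documents do not support that, for four reasons.

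- The type of ANOVA is open. The authors use paired methods elsewhere, so repeated-measures ANOVA is a natural reading. ANOVA might also be meant for a baseline factor with several levels, such as ethnicity.
- The inflated false-positive rates belong to a pooled arm comparison that the article does not propose. The trajectory test errs the other way.
- The large loss of power depends on an effect well below the stated 1.35 and, mostly, on moderate to high correlation under compound symmetry. At 1.35 power is about 90% or more, and under AR(1) the gap to the Hotelling test at 0.71 is modest.
- A two-sample t-test at one visit, or on change from baseline, is valid whatever the within-child correlation. The trajectory phrase could also be met descriptively by plotting visit means.

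It can also be said that covariance structure and model terms are commonly left to an analysis plan. That is right for those details, and their absence alone would be no finding. What stands against the reply is narrower: the article does assign a test to change in continuous outcomes, and that test compares neither arms nor more than two visits.

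**Conclusion.** The point holds as a mismatch between a stated aim and the stated methods: the six-visit trajectory has no named between-arm analysis that respects within-child correlation. This follows from the text alone and rests on no assumed figure.

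The numerical consequences are conditional. With visits as independent rows and correlations of 0.3 to 0.8, false-positive rates run to roughly 12–37% for a pooled arm comparison and from about 3.5% to below 0.1% for arm-by-visit. Power loss is substantial at about 0.71 SD in most settings examined and small at 1.35. If repeated-measures ANOVA is meant, the error rates are largely repaired; what remains is the loss of children with missed visits, which sits badly with the intention-to-treat promise. The wording should be changed, but it does not show that the trial's result will be wrong.

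**What to change.** For ALT, GGT and the other repeatedly measured continuous outcomes, replace the paired t-test and the unqualified t-test and ANOVA as the between-arm analysis. Use one linear mixed model for repeated measures with arm, categorical visit, arm-by-visit and baseline value, an unstructured within-child covariance, and a simpler structure named in advance as fallback. Report the between-arm difference at one pre-specified visit (for example week 48) as the main contrast and the joint arm-by-visit test for the trajectory. Keep paired t-tests as within-arm description only.

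The model uses the available visits of children with partial follow-up, under a missing-at-random assumption that should be stated. The cost is revised wording, slightly more programming and a few more covariance parameters to estimate from 64–80 children, which the fallback covers. No extra data or participants are needed.

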### Participant timeline

Baseline characteristics of the patient (e.g., age, gender, ethnicity, serum biomarkers, and BMI) will be collected.

### Sample size

Sample size estimation will be performed using Professional Association for SQL Server (PASS) 2014 software for grasp degree analysis (Power Analysis). The mean effect size of the lifestyle intervention on the improvement of ALT indicators (Effect size) was estimated to be −1.35 according to the Meta-analysis of the clinical study conducted by Utz-Melere et al. (14, 15). The sample size required will be 32 study subjects per group by power analysis in reaching 80% effectiveness, using a two-tailed test with a test level of 0.05. Based on a 20% failure rate, this part of the study required 80 subjects, 40 in each group.

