### Intervention

The interventions for the control group mainly consist of the routine distribution of health education materials and health education by holding health-themed lectures, and the preliminary proposed interventions are shown in Table 1.

**Table 1 T1:** Control group.

**Intervention**	**Intervention content and frequency**
Routine care	At each visit to the hospital, in this time, the child and his parents are given health education on diet and exercise booklets, and the parents supervise the child's daily life. The team members will review the child's condition every month for feedback.

To the above, the following four intervention components will be added, which shown in Table 2.

**Table 2 T2:** Intervention group.

**Intervention**	**Intervention content and frequency**
1. Establishing management teams	In addition to the subject leader, seven research team members will be each responsible for several participants (children with NAFLD) in need of intervention and formed a WeChat group for their parents.
2. Establishment of a nursing intervention team.	Composed of the Director of Nursing, a pediatric endocrinologist, a senior health lecturer and a nutritionist, three nurse leaders and a charge nurse with a master's degree. The director of the nursing department is the team leader. All members received half-month training from the team leader, including data collection, the purpose, model and implementation methods of the extended care intervention, and communication skills with the children and their parents. The training will be mainly in the form of intensive classes, and a theoretical examination will be conducted at the end of the training, requiring each member to pass.

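### The stated effect size of −1.35 gives about 10 per group at 80% power, not the stated 32, so the difference the trial was designed to detect is unclear

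*Protocol article*

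**What the plan says.** The Sample size section is the only place where the article justifies its 80 children. It gives these elements in turn:

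- The planning effect, for ALT: "Effect size) was estimated to be −1.35 according to the Meta-analysis of the clinical study". No SD, unit or raw mean difference is given.
- The result, with the power: "The sample size required will be 32 study subjects per group by power analysis in reaching 80% effectiveness".
- The test level: "using a two-tailed test with a test level of 0.05".
- The allowance for losses: "Based on a 20% failure rate, this part of the study required 80 subjects, 40 in each group".

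ALT is a named primary outcome in the Outcome section, so the calculation concerns an endpoint on which the trial will be judged. The Statistical analyses section lists the t-test and ANOVA among its methods. The Sample size section does not name the test used in the calculation and mentions no adjustment for multiplicity.

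**The concern.** An effect of 1.35 SD is very large, and detecting it takes few patients. A requirement of 32 per group at 80% power belongs to an effect about half that size. One of the three figures (effect, power or group size) must therefore be wrong, or −1.35 must be measured on a scale that the article does not describe.

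At stake is what the trial can be said to detect. An ethics committee, a journal or a later reader who repeats the calculation will not obtain 32, and cannot tell whether the sponsor planned for 1.35 SD, for about 0.71 SD, or for a difference in U/L.

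**Working it through.** **Inputs, all from the Sample size section:** effect size 1.35 in absolute value, read as a standardised mean difference because it is labelled an effect size and no SD is given; two-sided alpha 0.05; power 0.80; 1:1 allocation; stated n = 32 per group; 20% loss.

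**1. The plan's own figure.** By normal approximation, n per group = 2 × ((z₀.₉₇₅ + z₀.₈₀)/d)² = 2 × ((1.960 + 0.8416)/1.35)² = 2 × 2.075² = 8.6, so 9. The two-sample t-test (noncentral t) gives 9.67, so 10. The stated figure is 32, which is 3.2 times the t-test answer. It does not reproduce.

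**2. The loss step.** 32/(1 − 0.20) = 40 per group, 80 in total. This reproduces, so the discrepancy lies in the step from the effect size to 32. From 10 per group, the same step would give 10/0.8 = 12.5, so 13 per group and 26 in total.

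**3. Power at the stated size.** With n = 32 per group and d = 1.35, the t-test has power 0.9996.

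**4. Effect that fits the stated size and power.** Solving the t-test for n = 32 and power 0.80 gives d = 0.711.

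**5. Could another standard choice give 32?** Each row keeps d = 1.35 unless stated.

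| Variant | n per group |
|---|---|
| One-sided 0.05, 80% power (normal approximation) | 7 |
| Paired t-test, 80% power | 7 (pairs) |
| 90% power | 13 |
| 95% power | 16 |
| 99% power | 22 |
| Alpha 0.01, 80% power | 15 |
| Alpha 0.001, 80% power | 22 |
| Alpha 0.001, 90% power | 26 |
| Bonferroni over 10 tests, 80% power | 17 |
| Rank test instead of t-test, 80% power | 11 to 15 |
| Half the effect (0.675), 80% power | 36 (35 by normal approximation) |

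None gives 32.

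**6. Could −1.35 be a raw ALT difference?** Then 32 per group at 80% power needs SD = 1.35/0.711 = 1.90. The article states no such SD. As an illustration only, with SDs that I assume because the article gives none, the power at 32 per group for a difference of 1.35 U/L is:

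| Assumed SD (U/L) | d = 1.35/SD | Power |
|---|---|---|
| 10 | 0.135 | 8.3% |
| 20 | 0.068 | 5.8% |
| 40 | 0.034 | 5.2% |

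So the raw reading recovers 80% power only with an SD near 1.9, and the standardised reading gives over 99.9%.

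**The case against.** The strongest reply is that the mismatch is harmless. If 1.35 SD is the intended effect, 32 per group is more than enough, and the trial is not underpowered for it. That is right as far as it goes, and it limits the point: the documents do not support a claim that 80 children are too few. It does not rescue the statement, because 80% power is then wrong.

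A second reply is that an article condenses a fuller protocol, where the SD and the test may be given. That may explain missing detail, but not a printed result that conflicts with its printed inputs.

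A reader might infer three stronger things, and the documents do not carry them:

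- *That −1.35 is the wrong contrast, because controls also receive lifestyle education.* The section describes the figure as an effect of lifestyle intervention, and under Table 1 of the Intervention section "the child and his parents are given health education on diet and exercise booklets". But the article does not say what the comparators in the cited meta-analysis received. If they too had routine advice, the contrasts could be similar. This is a question for the sponsor, not an error shown.
- *That a null result would be misread as excluding an effect the trial was never designed for.* The article presents −1.35 as the planning effect, and with 99.96% power a null result would be strong evidence against 1.35 SD.
- *That 0.71 SD is the true design effect.* It is solved backwards from 32 per group, appears nowhere in the article and comes with no clinical rationale.

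Nor is there a basis for quoting a smaller detectable effect from a baseline-adjusted comparison. The Statistical analyses section uses analysis of covariance to ask whether baseline variables predict change, and does not specify it for the comparison between arms.

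**Conclusion.** The sample-size statement is arithmetically wrong as printed: its inputs require 10 per group (9 by normal approximation), not 32. This rests on reading −1.35 in SD units, as its label suggests, and on a two-group comparison of means. The raw-difference reading would need an unstated SD of about 1.9.

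The article cannot settle which figure is at fault. The conclusion is therefore limited to this: the sole justification for the sample size does not reproduce, and the difference the trial was designed to detect is unclear. It should be corrected, because ALT is a primary outcome and the correction is cheap.

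**What to change.** Keep 80 children, 40 per group. Retrieve the software inputs behind the 32 (effect measure, SD and its unit, test, power) and rewrite the Sample size section so that they agree. Two consistent statements are possible on the SD scale:

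- −1.35 SD is the design effect, and 32 evaluable children per group give power above 99.9% for it; or
- 32 evaluable children per group give 80% power, two-sided 0.05, for a difference of about 0.71 SD, and −1.35 is not the effect that yields 32.

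The choice should follow from the retrieved inputs, not from whichever statement fits the number more conveniently. If the inputs show that −1.35 was a raw difference, state its unit, the SD used and the source of that SD.

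The cost is one paragraph. Recruitment, conduct and analysis do not change.
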